#### Six-month follow-up

Six months after the fitting visit, we mailed the final set of outcomes questionnaires to participants. These were returned by postage-paid mail. The packet consisted of the SF-12, PHQ, EAR (Inner and Outer), HHIE, CPHI, AdHeRe, SADL, IOI-HA, and transitional QoL measure. If items were left blank, an RA attempted to obtain the information via telephone.

### Utilization and Cost Outcomes

We chose the 6-month interval after the hearing aid fitting to track utilization and cost variables because pilot data indicated that 75% of all unplanned visits occurred in this timeframe. Total costs will be the sum of costs of planned (fitting and follow-up) and unplanned (e.g., hearing aid repairs) audiology visits. We estimated the cost of fitting and follow-up visits based on provider time and pay grade. For unplanned visits, we estimated the cost of the visit using the cost for each CPT code associated with the visit from the VA cost accounting system. All cost estimates included fringe benefits and indirect and overhead costs.

### Data and Study Management

The study and all study modifications were approved by the Institutional Review Board of the University of Washington and the Research and Development Committee at VA Puget Sound Health Care System. RAs received thorough training in the process of informed consent, and their first enrollment interview received full edit reviews. Ten percent of all participant files were randomly audited for errors by the project manager. Data were entered into a Microsoft Access database using double-data entry verification.

### Analysis

The cohort description and baseline characteristics are described in this report using straightforward descriptive statistics. Future study results will use an intent-to-treat analysis. The primary purpose of this trial was to investigate the relative effectiveness of group and individual appointments in audiology. We used a factorial design with concurrent testing of group fittings and group follow-ups to facilitate insight into the value of a group format for both visits with one trial. The primary outcome of effectiveness was hearing-related function (Inner EAR) 6 months after the hearing aid fitting.

For our primary analysis, we will evaluate the overall effectiveness of group versus individual hearing aid fitting and group versus individual hearing aid follow-up for the Inner EAR using multivariate mixed model regression to adjust for factors related to hearing-related function and account for potential clustering among participants of a given group visit. Because our trial was a non-inferiority study, we will test the one-sided hypothesis that the effect of group visits does not lead to a detrimental effect beyond the clinically significant range. Secondary analyses will focus on secondary outcomes, and also on subgroup analyses for the primary outcome variable. Secondary outcomes will include hearing aid adherence, hearing handicap, communication strategies, and satisfaction with amplification. Subgroup analyses will focus on principal covariates such as use of monaural versus bilateral aids, sensorineural versus mixed hearing loss, degree of hearing loss, and the presence of specific hearing aid features such as directional microphones and telephone coils. The study was adequately powered to detect large differential treatment effects, but analyses of smaller effects will be exploratory rather than confirmatory.

Economic evaluation will estimate potential cost savings from the VA's perspective for group visits compared to individual visits. We will examine the effect of the group visit intervention on the number of unplanned visits and cost of unplanned visits. Although this study was not powered to definitively determine cost-effectiveness, exploratory calculations of the unit cost to obtain a successfully treated patient (an Inner EAR improvement of more than the minimally clinically important difference of 6.0 points) will be made. We will also conduct analyses with a secondary measure of treatment success: adherence to hearing aid use (the cost to obtain an adherent patient, and the cost to obtain an additional hour of adherence per day).

### Sample Size

We estimated our sample size based on a minimum clinically significant difference in Inner EAR scores of 6.0 points on a 100 point scale with standard deviation of 23.5, and a conservative loss to follow-up of 20%. We controlled for possible provider effects, site, and treatment, and accounted for most sources that induce clustering, and thus anticipate weak (<.10) within-group correlation. Enrollment of 660 participants (330/arm) would yield 90% power (and an alpha error of 5%) to reject the one-sided null hypothesis. An important consideration was to ensure that we had adequate power to detect changes in secondary outcomes, such as decreases in dichotomous hearing aid adherence. Using a sample size of 264 analyzable participants in each arm and our baseline adherence rate of 95%, we will have 92% power to ensure that hearing aid adherence rates do not worsen more than 10% (relative percentage).

Our study design was a factorial trial evaluating two interventions. This has the benefit of research economy and the ability to test for non-additive effects for the two interventions. For our research questions we chose not to make a multiple comparison adjustment since we are prepared to make separate conclusions for each of the two interventions. A multiple comparison correction is appropriate whenever a single conclusion is derived from the evaluation of multiple tests. We will make separate conclusions regarding group versus individual hearing fitting and regarding group versus individual follow-up.

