#### Group fitting

For the group fitting, up to three participants received individual programming during one 45-minute period. They then waited while a second set of up to three participants received programming during a second 45-minute session. Then, these six participants and their guests convened for a 60-minute group orientation in a quiet conference room in or near the audiology clinic. The orientation was conducted by a hearing aid technician or audiologist. Teaching topics included: how a hearing aid works; use, care, and maintenance; acoustic feedback; battery use, replacement, and ordering; telephone use; warranty and repairs; listening and communication strategies; and realistic expectations. Functions of special features covered during the individual portion of the visit were reviewed. The format was standardized and facilitated by a PowerPoint presentation combined with hands-on practice. Participants also received a handout of the PowerPoint presentation. An example of the timing of a typical group hearing aid fitting is shown in Table 3. In this scenario, 4.5 hours of audiologist time and 1 hour of audiologist or technician time was used to see up to six participants.

**Table 3 T3:** Group hearing aid fitting clinic schedule.

HAF appointment	Duration	Audiologist A	Audiologist B	Audiologist C	Technician or Audiologist
Individual Programming	45 minutes	Patient #1	Patient #2	Patient #3	

Individual Programming	45 minutes	Patient #4	Patient #5	Patient #6	

Group Orientation	60 minutes	--	--	--	Patients #1-6

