#### Group follow-up

This visit was scheduled with up to five participants during a 75-minute sessions, 45 minutes of which reviewed information covered at the hearing aid orientation, and covered the effects of acquired hearing loss, coping with hearing loss, pinpointing the source of communication problems, realistic expectations, management of difficult communication situations, guidelines for hard of hearing, and guidelines for significant others. These visits were conducted by one of the staff audiologists in the same quiet conference room in or near the audiology clinic as the group orientation visits. This session was facilitated by a PowerPoint presentation, and participants were provided with a handout of the presentation. Individual adjustments, if needed, were conducted during the 30 minutes after the group portion. In this scenario, 75 minutes of audiologist time was used to see up to five participants (Table 5). For some weeks, the five-person group was not filled resulting in a smaller group size.

**Table 5 T5:** Group hearing aid follow-up clinic schedule.

Follow-up appointment	Duration	Audiologist A	Audiologist B	Audiologist C
Group	75 minutes	Patients #1-5	--	--

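### The stated 90% power for the Inner EAR is the figure without clustering; at the article's own ceiling on within-group correlation it is about 85–86%

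*Protocol article*

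**What the plan says.** The Sample Size section of the protocol article builds on a "minimum clinically significant difference in Inner EAR scores of 6.0 points on a 100 point scale". The SD is taken as 23.5, and one participant in five is expected to be lost. The section says that provider, site and treatment were controlled for, and that the investigators "thus anticipate weak (<.10) within-group correlation". It then concludes: "Enrollment of 660 participants (330/arm) would yield 90% power (and an alpha error of 5%) to reject the one-sided null hypothesis". The adherence calculation in the same section uses 264 analysable participants per arm, which is 330 × 0.80. No design effect, group size or inflation factor is given.

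The group visits are the source of the clustering. Under Group fitting, up to three participants are programmed in each of two periods and then "these six participants and their guests convened for a 60-minute group orientation". Under Group follow-up, "This visit was scheduled with up to five participants", and some groups were not filled. Under Analysis, the primary mixed model is to adjust for factors related to hearing function and to "account for potential clustering among participants of a given group visit".

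**The concern.** The article acknowledges a correlation, bounds it and commits the primary analysis to allowing for it, but the power figure appears to leave it out. Calling a correlation below .10 weak does not make it negligible. The variance penalty depends on the correlation multiplied by group size minus one, so at .10 even four or five analysable members per group raise the variance of the group-arm mean by 30–40%.

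What is at stake is how the trial is read. In a non-inferiority trial an inconclusive result is partly judged against the stated power, and the Discussion repeats that the study was powered for clinically significant differences in hearing-related function. If the 90% holds only with zero correlation, the chance of missing true non-inferiority is understated.

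**Working it through.** **Inputs.** Margin 6.0, SD 23.5, one-sided alpha 5%, loss 20%, 330 enrolled and 264 analysable per arm, correlation (ICC) below .10 (all Sample Size). Group sizes of up to six (Group fitting) and up to five (Group follow-up). The article does not state the true difference under the alternative; I assume 0.

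**Step 1: reproduce the stated figure.** With independent observations,

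n per arm = 2 × [23.5 × (1.645 + 1.282) / 6]² = 262.7, so 263.

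263 / 0.80 = 329, against the stated 330. At 264 per arm:

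- SE = 23.5 × √(2/264) = 2.045
- power = Φ(6/2.045 − 1.645) = Φ(1.289) = 90.1% (a noncentral t calculation also gives 90.1%)

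The 20% loss accounts for the whole step from 330 to 264, and 264 is just enough for 90% with no correlation. One-sided 2.5% does not reproduce the figure: it needs 323 analysable per arm and gives 83.5% at 264.

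**Step 2: could an allowance be hidden in the 330?** If all 330 per arm were analysed with a group-arm design effect of 1.5 (six per group, ICC .10), then (1 + 1.5)/330 = 2/264, which also gives 90.1%. That reading leaves nothing for the 20% loss and contradicts the 264 analysable per arm in the same section.

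**Step 3: add the clustering.** Individual visits are not clustered, so only the group arm is inflated:

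- DE = 1 + (m − 1) × ICC
- SE = 23.5 × √((1 + DE)/264)
- power = Φ(6/SE − 1.645)

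Because 264 is a count after loss, m must also be after loss: 6 × 0.80 = 4.8 for fitting and 5 × 0.80 = 4 for follow-up.

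| ICC | Fitting, m = 4.8: DE | Power | Follow-up, m = 4: DE | Power |
|---|---|---|---|---|
| .10 | 1.38 | 85.2% | 1.30 | 86.2% |
| .05 | 1.19 | 87.7% | 1.15 | 88.2% |
| .02 | 1.076 | 89.1% | 1.06 | 89.4% |

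For example, at ICC .10 and m = 4.8, SE = 23.5 × √(2.38/264) = 2.231 and power = Φ(2.689 − 1.645) = Φ(1.044) = 85.2%.

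**Step 4: sensitivity to uneven loss.** If loss falls at random on individuals, groups end up unequal. An analysed member of a full group of six then has on average 5 × 0.80 = 4 analysable companions, so DE = 1 + 4 × .10 = 1.40 and power is 84.9%. For groups of five, DE = 1 + 3.2 × .10 = 1.32 and power is 86.0%. The range of about 85–86% stands.

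**Step 5: what covariate adjustment would have to deliver.** To bring the SE back to its unclustered value at ICC .10, the residual variance must fall by the factor 2/(1 + DE):

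- fitting: 2/2.38 = 0.84, a 16% reduction, or a residual SD of 23.5 × √0.84 = 21.5
- follow-up: 2/2.30 = 0.87, a 13% reduction, or a residual SD of 23.5 × √0.87 = 21.9

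**The case against.** The strongest reply has three parts.

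- **Clustering was not overlooked.** The article names it, explains why it should be weak, bounds it and puts it into the primary model. This stands. The validity of the planned test is not in question; only the power figure is.
- **The correlation and group sizes are maxima.** The .10 is a ceiling, groups are described as up to six or five, and some follow-up groups were under-filled. This also stands, and it places 85–86% at the unfavourable end.
- **The mixed model may gain as well as lose.** It also adjusts for factors related to hearing function, and a 13–16% reduction in residual variance would restore 90% even at ICC .10. The baseline Inner EAR SDs in Table 9 (13.1 to 14.7) are not six-month SDs, but they give no sign that 23.5 is too small. This limits what can be said about the power actually achieved. It does not rescue the stated calculation, which uses the full 23.5 and claims no such gain.

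A reader might also infer more than the article supports:

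- **Power of 83.6%, with up to a 16% chance of missing non-inferiority.** This takes 264 per arm after loss but leaves all six members of every group analysable. The two inputs do not belong together.
- **The primary test is certainly weaker than stated.** That needs zero covariate gain, which the article neither asserts nor excludes.
- **The model misses one of the two kinds of group visit.** The article does not specify a single group effect, and the random-effects structure is a matter for the analysis plan, which is not shown.

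**Conclusion.** The point holds as a correction to one stated figure. The 90% is the power for independent observations, and it does not fit the correlation that the same section anticipates. On the article's own inputs it should read about 85–86% at the .10 ceiling, 88% at .05 and 89% at .02, a shortfall of 1 to 5 percentage points. At the ceiling, the chance of missing true non-inferiority is about 14–15% rather than 10%.

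This rests on a true difference of 0, full groups reduced only by the planned 20% loss, inflation of the group arm alone, no covariate gain, and no added term for clustering from the other factor's group visits, which runs across both arms of each comparison. That no allowance was made is inferred: the article does not say so, but its figures reproduce without one.

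The severity is minor. Enrolment is complete, power stays above 80% throughout, and no margin, estimate or decision rule changes.

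**What to change.** Amend the power sentence in Sample Size in one of two ways:

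- give the power as about 85–89% for a within-group correlation of .10 to .02, stating the design effects (1.38 and 1.30 at .10) and the analysable group sizes (4.8 and 4) behind it; or
- keep 90% and say that it assumes either no clustering or an offsetting gain from covariate adjustment, with the gain assumed.

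This costs one sentence and a slightly less favourable stated power. No more participants are needed. For scale only, holding 90% at a correlation of .10 would have taken 2.38/2 × 262.7 = 313 analysable per arm for fitting and 2.30/2 × 262.7 = 303 for follow-up, or about 391 and 378 enrolled, against 330.

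### The 92% power stated for hearing aid adherence does not follow from its stated inputs, which give over 99% as a non-inferiority test; the error is conservative

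*Protocol article*

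**What the plan says.** The Sample Size section of the protocol article sizes the trial on the Inner EAR: a 6.0-point difference, a standard deviation of 23.5 and 20% loss to follow-up. "Enrollment of 660 participants (330/arm") "would yield 90% power (and an alpha error of 5%) to reject the one-sided null hypothesis". The section expects a within-group correlation below 0.10 but states no design effect.

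It then turns to adherence. The lead-in sentence speaks of having enough power to pick up decreases in dichotomous adherence. The inputs follow: "Using a sample size of 264 analyzable participants in each arm and our baseline adherence rate of 95"%. The result is "we will have 92% power to ensure that hearing aid adherence rates do not worsen more than 10% (relative percentage").

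For this figure the section gives no test, significance level, assumed true adherence in the group arm or design effect. The abstract lists adherence among the primary outcomes, whereas the opening of Methods and the Analysis section treat it as secondary.

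**The concern.** The sentence gives a sample size, a reference rate and a margin, and it is worded as non-inferiority in a trial that describes itself as a non-inferiority trial with one-sided testing. A reader should be able to recover 92% from those inputs and cannot: they give well over 99%.

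The section calls adequate power for secondary outcomes an important consideration, and this is the only secondary outcome for which it gives a figure. As it stands, the reader cannot tell whether the 92% is a slip, belongs to a different test, or contains a clustering allowance that the primary figure beside it does not. What is at stake is the accuracy and reproducibility of a stated power, not the adequacy of the sample.

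**Working it through.** **Inputs**

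- From Sample Size: 264 per arm (330 × 0.80), adherence 95%, margin 10% relative. The margin is 0.10 × 95 = 9.5 points, that is, a fall to 85.5%.
- Assumed: one-sided 5%, which is stated for the Inner EAR and not repeated for adherence.
- Assumed: equal true rates for the non-inferiority reading. The opening of Methods hypothesises equal or better adherence with group visits.
- For the clustering checks: correlation at its stated ceiling of 0.10, with groups of up to six (Group fitting) and up to five (Group follow-up). The design effect 1 + (m − 1) × 0.10 is then 1.5 and 1.4.

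Φ is the standard normal distribution function.

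**1. The primary figure in the same section**

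SE = 23.5 × √(2/264) = 2.045. Power = Φ(6.0/2.045 − 1.645) = Φ(1.289) = 90.1%. The stated 90% reproduces, with no design effect.

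**2. Adherence as worded (non-inferiority, equal rates)**

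SE = √(2 × 0.95 × 0.05/264) = 0.01897. Power = Φ(0.095/0.01897 − 1.645) = Φ(3.363) = 99.96%.

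| Variant | Power |
|---|---|
| One-sided 2.5% | 99.88% |
| Restricted null variance, one-sided 5% | 99.87% |
| Log risk ratio, margin 0.90, one-sided 5% | 99.99% |
| Design effect 1.5, group arm only, one-sided 5% | 99.8% |
| Design effect 1.5, both arms, one-sided 5% | 99.3% |

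On this reading 92% power needs (1.645 + 1.405)² × 2 × 0.95 × 0.05/0.095², or about 98 per arm, not 264.

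**3. Adherence as detection of a fall from 95% to 85.5%, no clustering**

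The mean rate is 0.9025. The null SE is √(2 × 0.9025 × 0.0975/264) = 0.02582. The alternative SE is √((0.95 × 0.05 + 0.855 × 0.145)/264) = 0.02549.

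- One-sided: Φ((0.095 − 1.645 × 0.02582)/0.02549) = Φ(2.061) = 98.0%. With continuity correction it is 97.2%.
- Two-sided: Φ((0.095 − 1.960 × 0.02582)/0.02549) = Φ(1.742) = 95.9%. Fisher's exact test gives 95.5%, and the continuity correction gives 94.4%.

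The nearest unclustered result is therefore 94.4%.

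**4. What does reach about 92%**

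For a design effect in both arms, both standard errors in step 3 are multiplied by its square root.

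| Added input | Power |
|---|---|
| Detection, one-sided, design effect 1.4 in both arms | 93.1% |
| Detection, one-sided, design effect 1.5 in both arms | 91.6% |
| Detection, two-sided, design effect 1.2 in both arms | 92.2% |
| Detection, two-sided, design effect 1.4 in group arm only | 91.4% |
| Non-inferiority, one-sided 5%, true group-arm rate 92% | 91.8% |

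In the last row the distance to the margin is 0.095 − 0.03 = 0.065 and SE = √((0.95 × 0.05 + 0.92 × 0.08)/264) = 0.02142, so power = Φ(0.065/0.02142 − 1.645) = Φ(1.390).

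Each row uses something that the section does not state for the adherence figure.

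**The case against.** The strongest defence is that 92% need not be a mistake. The lead-in sentence talks of detecting decreases, the same section mentions a correlation below 0.10, and group sizes of five or six appear in Methods. Put together, these give 91.6 to 93.1% one-sided, close to the stated value. This stands as a possible origin, and a reader who concluded that no calculation at 264 per arm gives 92% would be wrong. It does not make the sentence correct as written. The sentence names a non-inferiority criterion and no design effect, and the one-sided version needs the inflation in both arms: with 1.5 in the group arm only it gives 94.5%. The primary 90% beside it includes no such inflation.

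A second defence is that the discrepancy is harmless. In direction, it is. Power is understated, the sample size came from the Inner EAR, and no test is weakened.

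A reader might go further and infer that the 92% hides a loose margin, which should be tightened to about 6 points because 264 per arm could support that. The documents do not support this inference. The margin is stated openly, and 85.5% follows from it directly. What loss of adherence is tolerable is a clinical judgement that spare power does not settle, and the change would come after enrolment had closed. Nor is it free. Wald power at 6 points is 93.6% unclustered, but 88% with a design effect of 1.5 in the group arm, 83% with it in both arms, and 81% unclustered if true group-arm adherence is one point lower.

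**Conclusion.** The point holds as a correction to a stated power. On the inputs given, the non-inferiority power for adherence is above 99%, against the stated 92%, and clustering at the section's own ceiling does not change that. The detection reading without clustering gives 94 to 98%, depending on sidedness and continuity correction.

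This rests on two assumptions that the section leaves open: the one-sided 5% level applies to adherence, and true rates are equal. The first hardly matters, since one-sided 2.5% gives 99.88%. The second does, since a true group-arm rate near 92% would produce the stated figure, but the document assumes no such decline.

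The error is conservative. It casts no doubt on the number enrolled or on the adherence margin.

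**What to change.** Do one of the following in the Sample Size section:

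- Restate the adherence power as above 99% for a 9.5-point margin (95% to 85.5%) with 264 per arm, equal true rates and one-sided 5%.
- If 92% came from another calculation, replace the sentence with that calculation, giving the test, significance level, assumed group-arm adherence and any design effect.

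In either case, put the adherence and Inner EAR powers on the same clustering basis and say what it is.

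The first option costs one sentence and changes no patient number, margin or analysis. The second has one consequence to expect. If the 92% does contain a design effect, the Inner EAR figure must be re-derived with it and will fall below 90%. For example, 1.5 in both arms gives Φ(6.0/(2.045 × √1.5) − 1.645) = Φ(0.750), about 77%, before any gain from covariate adjustment.
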